#### Ancillary analyses

We will conduct effect modification analyses by introducing interaction covariates into the regression models with respect to age, gender, HBTQ, and each respective outcome at baseline. The posterior probability of interaction effects and the Watanabe-Akaike information criterion (WAIC) will be used for scientific inference from the effect modification models.

Systematic attrition to follow-up at the different time intervals will be studied by estimating the odds ratio of not responding conditional on age, gender, HBQT, and the two co-primary outcome variables measured at baseline.

#### SWAT analyses

To study the effects of the adaptive treatment strategy (ATS), meaning that participants who do not improve by the third week in treatment are randomized to extra support, based on primary outcomes, we will estimate the same multilevel models as in the primary outcome analyses but include only participants randomized to guided or unguided trial arms, for whom extra support was indicated. We will replace the time-by-group contrast in the multilevel models with a time-by-SWAT contrast and add an adjustment for main contrast group (guided vs. unguided). Exploratory analyses will add an additional interaction with main contrast group (time-by-group-by-SWAT) to estimate the differential effect of extra support conditional on guided or unguided mode of intervention delivery.

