21. *TIC-P* Healthcare consumption and productivity loss in patients with a psychiatric disorder (56 items); Bouwmans et al., 2013 [56]

22. *CSQ* Client Satisfaction Questionnaire (8 items), Attkisson & Zwick 1982 [57]

22.1. *CSQ, adapted* Client Satisfaction Questionnaire (8 items), adapted for mid-Tx assessment

23. *NEQ* Negative treatment effects questionnaire (20 items), Rozental et al. 2019 [58]

24. *Qualitative interview* Qualitative interview on experience of treatment intervention

The algorithm will build on data from the PHQ-9 and GAD-7 questionnaires, where data for all three timepoints will be entered for each questionnaire separately, as follows: [(T0 + T1)/2] − T2. If the outcome of the algorithm is equal to £0 for either PHQ-9 or GAD-7, or both, the participant will be randomized to the ATS, or to continue in the treatment arm to which they were assigned at the start of the main trial. See under “Interim analyses (21b)” for a more detailed description. Randomization will be conducted via SPSS version 28.0 using an outcome of the exact number of randomized individuals, stratified by group allocation to guided or unguided treatment. Participants with missing data at any of these timepoints will not be included in the SWAT since unsuccessful attempts will have already been made to encourage them to respond, and dropout from the main trial seems likely.

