## Analysis

### Statistical methods for primary and secondary outcomes (20a)

We will keep participants in the groups to which they were randomized in all analyses (intention-to-treat). We will conduct both available data analyses and analyses with missing data imputed using multiple imputations with chained equations (generating 200 datasets using 30 iterations of predictive mean matching). Both available data and imputed data analyses will be used to interpret findings.

All models of primary and secondary outcomes will be estimated using both Bayesian inference and maximum likelihood estimation [59]. The former will estimate the posterior distribution over effect estimates, while the latter will be used for null hypothesis testing. We will use (half) Student’s *t* priors for covariates, fixed intercepts, and error terms (centered at 0, with a scale of 2.5 and 3 degrees of freedom). Adaptive intercepts in multilevel models will be given standard normal priors. For point estimates, we will report the median of the posterior distribution of each parameter of interest (i.e., group contrasts), along with 95% compatibility intervals defined by the 2.5 and 97.5% percentiles of the posterior distributions. We will use the posterior probability of effect and *P*-values for our scientific inference.

The two co-primary outcomes, anxiety and depression, will be standardized and modeled using a multilevel linear regression model. The models will include a time-by-group interaction with time modeled as a dummy categorical variable (0 = T3, 1 = T4, 2 = T5, 3 = T6), as will group (0 = waiting list, 1 = unguided, 2 = guided). The models will be adjusted for baseline (T1) measures of the outcome variables (respectively) using a baseline-by-time interaction term and further adjusted for age, gender, and a binary variable indicating HBTQ (0 = No, 1 = Yes). Adaptive intercepts will be added to the models at the participant and university level. The linear combination of coefficient estimates for the group and time-by-group covariates will be used as effect estimates (i.e., differences between groups at the different follow-up intervals). For our primary contrasts (guided vs. waiting list and unguided vs. waiting list), we will report effects at T3 and T4. For our exploratory contrast (guided vs. unguided), we will report effects at all four follow-up intervals.

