### Methods for additional analyses (e.g., subgroup analyses) (20b)

#### Mediator models

We will estimate the mediated effects of the guided and unguided interventions (vs. waiting list) with respect to two potentially mediating factors (behavioral activation-depression and managing negative thoughts). We will use a causal inference framework, using Bayesian inference to estimate the natural direct effect and natural indirect effect (as per the definitions of Pearl [60]). We will report on the posterior distributions of these two effects. For each primary outcome (anxiety and depression), we will estimate mediation models for each mediator separately, as well as one model with both mediators. Mediator measures will be standardized and modeled using linear regression, using the same adjustments as in the primary outcome models (i.e., outcomes measured at baseline, age, gender, and a binary variable indicating HBTQ). The mediation models will estimate both the mediated effects from T2 mediators to T3 outcomes, and T3 mediators to T4 outcomes.

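### The SWAT models adjust for the T1 score only and leave out the T2 score, which is the SWAT's own pre-randomization measure

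*Protocol article*

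**What the plan says.** Under SWAT analyses, the protocol article takes over the primary-outcome model: "we will estimate the same multilevel models as in the primary outcome analyses but include only participants randomized to guided or unguided trial arms", limited to those for whom extra support was indicated. It then lists what changes: "We will replace the time-by-group contrast in the multilevel models with a time-by-SWAT contrast and add an adjustment for main contrast group". An exploratory analysis adds a three-way interaction with main arm. No other covariate is mentioned.

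The inherited model is set out under Statistical methods for primary and secondary outcomes (20a). On the baseline score it says: "The models will be adjusted for baseline (T1) measures of the outcome variables (respectively) using a baseline-by-time interaction term". Age, gender and HBTQ are the other covariates. The outcome times are T3 to T6, so T2 is not an outcome time either.

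Under Procedure for inclusion in the SWAT and Interim analyses (21b), entry depends on the T2 PHQ-9 and GAD-7 compared with the T0 and T1 scores. A participant qualifies if the mean of T0 and T1, minus T2, is zero or less on at least one scale. T2 is thus measured before the SWAT randomization. It is also complete by design: "Participants with missing data at any of these timepoints will not be included in the SWAT".

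**The concern.** The SWAT is a second randomization, carried out at week 3. For that comparison the last score before randomization is T2; T1 predates the main randomization and the first three weeks of treatment. In a randomized comparison, the pre-randomization value of the outcome is normally the first covariate to include. It removes outcome variance that it can predict, and it corrects any chance difference between the ATS and continued-treatment groups in where they stood when they were split. The model as written carries T1 across and does not use T2 at all, although every SWAT participant has it.

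What is at stake is the width of the interval around the SWAT effect, in a comparison planned on far fewer participants than the main trial.

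**Working it through.** **The plan's own figure.** Sample size (14) gives d = 0.4 and 100 + 100 at-risk participants. Alpha 0.05 two-sided and power 0.80 are stated for the main trial and assumed here for the SWAT. With n per arm = 2(1.960 + 0.842)²/d², the result is 2 × 7.849/0.16 = 98.1, so 99. The t-test solution is 99.08, so 100 per arm (power 0.804). The figure reproduces and uses no covariate.

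**Effect of a covariate.** With adjustment, n per arm = 2 × 7.849 × (1 − R²)/d². Here R² is the share of outcome variance explained by the covariates and d is kept in units of the unadjusted SD. The variance ratio from adding T2 to T1 is (1 − R² with T1 and T2)/(1 − R² with T1).

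**Inputs that the documents do not give.** All correlations are assumptions. Normal scores were simulated for T0, T1, T2 and one follow-up on both scales, with:
- T0-T1, T1-T2, T1-outcome and T2-outcome correlations as in the table;
- T0 correlations with T2 and with the outcome at 0.93 times those of T1;
- a PHQ-9/GAD-7 correlation of 0.5;
- a mean improvement of 0.3 SD by T2.

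The entry rule, in its averaged form, was applied to both scales. About half (49-51%) qualified, and R² was computed among them only.

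| T0-T1 / T1-T2 / T1-outcome / T2-outcome | R², T1 | R², T1+T2 | Variance ratio | n per arm, T1 → T1+T2 | Power at 60 per arm |
|---|---|---|---|---|---|
| 0.70 / 0.60 / 0.50 / 0.50 | 0.260 | 0.313 | 0.928 | 73 → 68 | 0.72 → 0.75 |
| 0.70 / 0.60 / 0.45 / 0.50 | 0.216 | 0.284 | 0.914 | 77 → 71 | 0.70 → 0.74 |
| 0.70 / 0.60 / 0.50 / 0.60 | 0.274 | 0.387 | 0.845 | 72 → 61 | 0.73 → 0.80 |
| 0.70 / 0.60 / 0.40 / 0.60 | 0.192 | 0.348 | 0.807 | 80 → 64 | 0.68 → 0.77 |
| 0.70 / 0.65 / 0.50 / 0.65 | 0.279 | 0.423 | 0.801 | 71 → 57 | 0.73 → 0.82 |
| 0.75 / 0.70 / 0.50 / 0.70 | 0.289 | 0.474 | 0.740 | 70 → 52 | 0.74 → 0.86 |

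Worked line (third row): (1 − 0.387)/(1 − 0.274) = 0.613/0.726, about 0.845; n goes from 98.1 × 0.726 = 71.2 (72) to 98.1 × 0.613 = 60.1 (61).

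The reduction in residual variance runs from 1 − 0.928 = 7% to 1 − 0.740 = 26%. With 100 per arm, power rises from 0.88-0.92 with T1 to 0.92-0.97 with T1 and T2. The 60-per-arm column applies the main trial's 40% attrition at T4 to 100 per arm (100 × 0.6). It is an illustration, because the SWAT figure states no attrition.

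**Is T2 the better single covariate?** In the first row T2 alone gives R² = 0.269 against 0.260 for T1 alone, a negligible gap. T2 pulls clearly ahead only when it correlates more strongly with the outcome than T1 does.

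**The case against.** The strongest answer is that this is a choice of efficiency, not an error. The SWAT contrast is randomized, so a model with T1, demographics and main arm estimates it without bias when data are complete, and it matches the main analysis. T1 correlates with T2, so part of any chance T2 imbalance is already absorbed. All of this stands, and it limits the point to precision and residual imbalance. It does not give a reason to leave T2 out.

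Nor is this a detail deferred to an analysis plan. The article sets the baseline model by model: it moves to T0 for the DSM-5 CCSM because T1 is not collected. It makes no such change for the SWAT. The all-assessments analysis under Exploratory analyses concerns the primary outcomes generally and does not replace the SWAT model.

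Five stronger readings are tempting and are not supported:
- **That the SWAT is short of power.** The 100 + 100 reaches 80% unadjusted, and the document gives no expected number of at-risk participants. Attrition in the SWAT is a separate sample-size question.
- **That T2 is established as the best covariate.** This is inferred from its timing; no correlations are given.
- **That the gain is worth up to 34% more participants.** The closed form at correlations 0.50 (T1-T3), 0.65 (T2-T3) and 0.60 (T1-T2) gives R² = (0.25 + 0.4225 − 0.39)/0.64 = 0.441, a ratio of 0.559/0.75 = 0.745, and 1/0.745 = 1.34. But that formula ignores selection on T2 into the SWAT.
- **That omitting T2 biases the SWAT estimate through dropout.** This would need dropout to depend on T2 differently by group. The protocol does hypothesize better retention under the ATS, but says nothing about dependence on T2. It also plans multiple imputation without listing the variables used.
- **That the mediation models omit the baseline mediator and so inflate the indirect effect.** Mediator models describes the mediator regressions as "using the same adjustments as in the primary outcome models (i.e., outcomes measured at baseline, age, gender, and a binary variable indicating HBTQ". Because the primary model uses each outcome's own T1 value, this can be read as including the mediator's own T1 score in the mediator equation. Any size put on an inflation would rest on invented coefficients.

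**Conclusion.** The point holds as a modest, cost-free improvement. The SWAT model in the protocol article conditions on T1 and leaves out T2, although T2 precedes the SWAT randomization, determines entry and is complete for all who enter. The consequence is lost precision and weaker control of chance imbalance at T2; with complete data it is not bias.

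Under the assumed correlations the loss is roughly 7-26% of residual variance in the selected sample. The lower end applies when T2 predicts the outcome no better than T1. The simulation covers a single follow-up. If the T2-outcome correlation falls toward that of T1 by T4 to T6, the gain there would be smaller. The planned SWAT sample size is not shown to be wrong.

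**What to change.** In the SWAT models, add the T2 score of the respective outcome with a T2-by-time interaction, and keep T1 with its existing interaction. The T2 score of the other scale may be added as well, since either scale can trigger entry. Record the change before the analysts see outcome data by SWAT allocation. The cost is one or two covariates that are already collected and complete; no procedure, visit or sample size changes.

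As a secondary clarification only, state under Mediator models that each mediator's T1 value (BADS and SOCT-P, both collected at T1 according to Table 2) enters both the mediator and the outcome equations. This settles the wording at no cost.

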#### Exploratory analyses

This trial will generate additional data not analyzed in the primary analyses. These data will be used in exploratory analyses with the aim of producing evidence for future refinements of interventions and intervention delivery. These exploratory analyses include:A process evaluation of the interventions, including participants’ experiences of support, treatment expectancies, satisfaction and alliance, and any negative treatment effects. Specific treatment process outcomes for all RCT participants include treatment expectancy (CEQ), attitudes towards professional help (ATSPPHS), treatment alliance (WAI-SR for Internet treatment), treatment satisfaction (CSQ), and negative effects of treatment (NEQ); see Table 2.Treatment process is also measured in terms of completed treatment modules and % of completed skills practices. Trial process outcomes for all RCT participants concern adherence.To the assessment plan, measured in terms of % completed measures at post-treatment; SWAT adherence measures include % of participants who are randomized to receive additional therapist support for the remainder of the treatment period (weeks 4 to 8). For participants who have given their consent in the preceding WHO-WMH-ICS survey, secondary outcomes will also include annual data on students’ academic records via LADOK, the Swedish national documentation system of higher education outcomes, specifically academic success, changes in academic study focus, or interruption of studies. Qualitative interviews concerning experience of treatment outcome and treatment-seeking pathways will complement secondary outcome measurement.Additional trial process-related outcomes include overall treatment interest and uptake, measured in terms of the percentage (%) of participants who respond to the study invitation (interest) as well as participate in treatment (uptake).An analysis of primary outcomes using all measures from all assessments during the intervention period, and follow-up data, with time modeled as numeric rather than categorical as in the primary analyses (with and without quadratic term for time).

### Methods in analysis to handle protocol non-adherence and any statistical methods to handle missing data (20c)

We will conduct both available data analyses and analyses with missing data imputed using multiple imputations with chained equations (generating 200 datasets using 30 iterations of predictive mean matching). Both available data and imputed data analyses will be used to interpret findings.

### Plans to give access to the full protocol, participant-level data and statistical code (31c)

The full protocol is contained in the approved ethical application (in Swedish) and is available in the supplementary material. Requests for participant-level data should be directed to the principal investigator (PI), [name], [contact].

## Oversight and monitoring

### Composition of the coordinating center and trial steering committee (5d)

The trial steering committee meets weekly via encrypted Zoom. Additional research team meetings take place ad hoc every 1–3 months, and in-person meetings are held at least once a year for strategic planning.

### Frequency and plans for auditing trial conduct (23)

Trial conduct is actively monitored via the core research team’s weekly meetings. Our management structure for this trial is slim, and the Project Management Group meets once every week. This group also manages trial steering as well as data monitoring and ethics. In this trial, we have two primary endpoint measures of outcome, PHQ-9 and GAD-7. We considered GCP monitoring for this trial but opted out due to their requirement that we use one endpoint measure as a primary outcome.

### Plans for communicating important protocol amendments to relevant parties (e.g., trial participants, ethical committees) (25)

Changes to the protocol require that the PI address proposed amendments to the Swedish National Ethical Review Authority https://etikprovningsmyndigheten.se/en/. See item 24.

### Dissemination plans (31a)

Publication and conference presentation plans are regularly drawn up and revised as needed at the core research team’s weekly meetings. Trial results will be disseminated via publications, conferences, participating universities’ media platforms, and the project website, https://www.psyk.uu.se/Divisions/clinical-psychology/national-assessment-and-e-health-interventions-for-mental-health-problems-among-university-students/.

## Discussion

Reducing the treatment gap for Swedish university students is a matter of high priority, particularly since Swedish students have worse mental health problems compared to their peers not attending university [62]. This project conducts research on internet interventions and expands the reach of mental health treatment for students, since more participants can be treated per treatment provider than via in-person treatment. With time, dissemination of internet interventions into ordinary care via student mental health clinics can make such interventions for mental health issues far more widely accessible to the student group.

Two specific innovations in this study are worthy of note. Firstly, the internet intervention program we are evaluating is a transdiagnostic, tailored program focused on treatment of depression and/or generalized anxiety disorder (e.g., [36]), with some comorbidity. This is important because comorbidity is highly prevalent among university and college students and impairments in daily role tasks, associated with common mental health problems in this population, are more severe the greater the extent of comorbidity [63]. Secondly, this project will provide knowledge about what might be possible in Sweden to push mental health development forward, to improve societal health and well-being on a larger scale in the short- and long-term. The knowledge gained from the clinical trial described in this protocol will include primary outcome data from the main RCT, long-term follow-up of the guided and unguided groups, and analysis of the adapted treatment strategy evaluated in the SWAT, in addition to treatment and trial process data such as intervention adherence. We hope that our findings will contribute to expanded future access to treatment for university students, supporting student health clinics in meeting the challenges of providing evidence-based interventions for common mental health problems, for an ever-growing number of students. The qualitative studies will contribute to additional knowledge about student experiences of internet treatment.

An additional future benefit of this study is the generation of data that can be used to develop a precision treatment modeling method that can contribute to developing personally adapted treatment configurations. The predictors available will consist of a rich set of self-report variables found in prior studies to be predictors of response to CBT; e.g., socio-demographic factors; history, triggers, and symptom of mental disorders; comorbid disorders/symptoms; stress and adversity; and personality traits/temperament [64]. Such a model could potentially facilitate automated referral of larger numbers of university students with common mental health problems to a tailored, precision treatment that will increase the chances of their recovery, and enhance completion of studies, building of relationships and self-care.

### Clinical significance

The high potential for alleviating suffering from mental health problems during emerging adulthood, among university students, has been emphasized throughout the protocol. We hope that the intervention content can be transferable to an appropriate platform following conclusion of the trial, pending positive outcomes. We will continue to monitor any adverse effects of the intervention and continue to implement routines for clinical action in case of decline in participant stability while participating in the internet interventions, including waitlist control group participants.

## Trial status

Recruitment for a pilot study, reported separately, was completed on October 19, 2021. Recruitment for the main trial began in mid-March 2022 and will continue until statistical power is estimated to have been achieved. The current protocol is version 3, dated January 30, 2024.

## Data Availability

Data may be available to collaborators on request to the PI, [name], [contact].

## Abbreviations

ATS: Adaptive treatment strategy
CBT: Cognitive behavioral therapy
DMP: Data management plan
GAD-7: General Anxiety Disorders-7 questionnaire
GDPR: General Data Protection Regulation
ICBT: Internet-based CBT
PHQ-9: Patient Health Questionnaire-9
PI: Principal Investigator
RCT: Randomized controlled trial
SWAT: Study within a trial
WHO-WMH-ICS: World Health Organization, World Mental Health International College Student Initiative
